#### Inclusion and exclusion criteria

Patients must meet the criteria of the National Institute of Neurological and Communicative Disorders and Stroke – Alzheimer’s Disease and Related Disorders Association (NINCDS–ADRDA) for probable or possible Alzheimer’s disease [52]. Mixed Alzheimer’s and vascular dementia cases will also be included. Only cases of Alzheimer’s disease with a mild severity of dementia will be included, as determined by the Clinical Dementia Rating Scale (i.e., scores of 0.5 or 1) [53] and by the Mini Mental State Examination (i.e., scores of 20 or more) [54]. The patient must experience any non-cognitive symptom that motivates the acceptance of psychotherapeutic help. Typically, symptoms of depression, apathy, anxiety or irritability are present at the time of enrolment. A caregiver must be available to take part in most of the psychotherapy sessions. This is typically the partner, but a child or a good friend, who is able to take responsibility for reminding the patient about therapeutic tasks, is also accepted.

Exclusion criteria are a concomitant alcohol or drug addiction and a history of a malignant disease, severe organ failure, metabolic or haematological disorders, neurosurgery or a neurological condition, such as Parkinson’s disease, epilepsy, postencephalitic or postconcussional syndrome.

#### Informed consent

The objectives and goals and detailed information about the assessment and therapy, as well as the procedure of randomization, will be explained to the subjects. The information will also be given in printed form to the subjects. Written informed consent will be obtained from all participants and caregivers prior to inclusion. Patients who cannot give their informed consent will not be included in the study.

#### Withdrawal criteria

Participation in the study is voluntary. There are no negative consequences for non-participation or dropping out. Patients who deny participation or drop out will receive medical and psychosocial care as usual.

#### Sample size

Previous studies of the interventions for patients with mild Alzheimer’s disease included in our multicomponent treatment programme found small-to-medium effect sizes for depression outcomes (*d* = 0.4 to 0.6, corresponding to *f* = 0.2 to 0.3) [12, 15, 21, 43]. We base our sample size calculation on the assumption of a small-to-medium effect size for depression as measured using the Geriatric Depression Scale (*d* = 0.5, *f* = 0.25). The sample size was calculated using G*Power 3.1.0 software [55]. Assuming *α* = 0.05 and a test power 1 − β = 0.80, a total sample size of *n* = 44 is required to test condition × time interactions in an analysis of variance (ANOVA) with repeated measurements (*r* = 0.3). Since previous studies on CBT-based psychotherapy for caregivers of people with dementia found medium [21] or large [23] effect sizes on mood measures (depression, anxiety), this sample size should also be sufficient to find an effect of the intervention on caregiver’s mood. We assume a rather conservative rate of loss of 60 % from the screening of eligibility to the enrolment of subjects. Thus, we propose to start with approximately 120 patients and caregivers at the screening, which we expect to reduce to 50 at enrolment. A drop-out rate of approximately 10 % would lead to *n* = 44.

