#### Engagement in pleasant or structured activities

Teri et al. [12] reported empirical evidence from a controlled clinical trial of two CBT-based interventions to treat depression in people with Alzheimer’s disease. One treatment involved increasing engagement in pleasant activities and events and the other involved behavioural problem-solving strategies. The participants in both intervention groups showed significant improvements in depressive symptoms compared with those in the two control groups, and these improvements were maintained for 6 months after the trial. The ‘pleasant events’ treatment resulted in a large effect size (*d* = 0.9–1.7 for three different depression measures), with 52 % clinically significant improvement (versus 20 % in the control groups). In addition, there were also significant improvements in caregivers’ depression scores, but no improvement for the caregivers in the control groups. Increasing engagement in pleasant activities, including social, physical and leisure activities, is not only important for reducing depression, but also decreases the amount of daytime sleep taken, improves night-time sleep [13] and reduce wandering, aggression and agitation [14].

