### Rationale for the current study

The current study combines theory-based, multicomponent intervention strategies, whose efficacy has been demonstrated in randomized controlled trials or supported by case studies, with state-of-the-art trial methodology. The study tries to overcome the shortcomings of previous research in several respects: (1) the interventions are based on established psychological models; (2) CBT strategies will be consistently applied; (3) a high quality of treatment and consistency in treatment delivery will be ensured by using trained psychotherapists with specialized training in the intervention programme and regular supervision during the study; (4) the targets of the interventions will be the patient with Alzheimer’s disease, the caregiver and the dyad; (5) the treatment will be structured, but also individualized according to individual problems; (6) a randomized, controlled, assessor-blinded study design will be employed; (7) various outcome measures, involving various domains of the patient’s and caregiver’s health, will be applied; (8) statistical power calculations will be used to estimate the sample size.

A modular and non-uniform programme is justified because no single strategy would achieve the treatment goal to the desired extent. Modular programmes are also common for other mental disorders, e.g. dialectical behavioural therapy for treating borderline personality disorder or CBT for treating depression.

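### The sample size enters d = 0.5 as f = 0.25 (the two-group rule f = d/2) in a condition × time interaction test, so 44 completers do not give the stated 80% power for d = 0.5

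*Protocol article*

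**What the plan says.** The Sample size section of the protocol article gives the range from earlier studies as d = 0.4 to 0.6, equates it with f = 0.2 to 0.3, and cites four sources, reference 12 among them. It then assumes a "small-to-medium effect size for depression as measured using the Geriatric Depression Scale" of d = 0.5, again equated with f = 0.25. The calculation was done in G*Power. "Assuming *α* = 0.05 and a test power 1 − β = 0.80", a total of 44 "is required to test condition × time interactions in an analysis of variance (ANOVA) with repeated measurements", with r = 0.3. Enrolment of 50 allows for a drop-out of about 10%. Neither the number of measurements entered nor a nonsphericity value is given.

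The Statistical analysis section plans ANOVAs of depressive symptoms with baseline depression among the covariates, growth curves, and four assessments (pre-test, post-test, two follow-ups).

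The Rationale section lists that "statistical power calculations will be used to estimate the sample size" among the ways in which the study improves on earlier research. In the Background, the subsection on pleasant or structured activities says of reference 12 that its pleasant-events "treatment resulted in a large effect size", namely d = 0.9 to 1.7 on three depression measures.

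**The concern.** The pairs 0.4/0.2, 0.5/0.25 and 0.6/0.3 all follow f = d/2. That is Cohen's f for the difference between two group means. The test being sized is a different one, the condition × time interaction. There, a group difference that appears only after baseline is spread over all cells of the design, so the same d gives a smaller f. Entering 0.25 as the interaction f sizes the trial for a larger effect than the one named.

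At stake is the stated justification for the sample size. Readers are told that the trial has an 80% chance of detecting d = 0.5 on a primary outcome scale. If the real figure is far lower, both the planned precision and any later result will be judged against the wrong benchmark.

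**Working it through.** **Inputs from the protocol article.** Alpha 0.05, target power 0.80, d = 0.5, f = 0.25, r = 0.3, n = 44 (Sample size); 1:1 allocation, so 22 per arm (Randomization); four assessments and baseline depression as a covariate (Statistical analysis).

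**Assumptions of mine.** d is a between-arm difference in cross-sectional SD units, the arms do not differ at baseline, the SD is equal at all visits, and r is the same between all pairs of visits.

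**1. The plan's own figure.** For the within-between interaction with k = 2 groups, m measurements and nonsphericity ε, G*Power's default formula is

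λ = f²·N·m·ε/(1 − r), df1 = (m − 1)ε, df2 = (N − 2)(m − 1)ε.

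With f = 0.25 and r = 0.3:

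| m | ε | smallest even N for 80% | power at N = 44 |
|---|---|---|---|
| 2 | 1 | 46 | 78.2% |
| 3 | 1 | 38 | 86.5% |
| 4 | 1 | 32 | 92.1% |
| 3 | 0.8 | 44 | 80.2% |
| 4 | 0.65 | 44 | 81.2% |

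So 44 is attainable when f = 0.25 is entered directly as the interaction effect. The settings cannot be identified from the text.

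**2. The f that d = 0.5 implies, pre/post.** The cell means are 0 and 0 (control), 0 and 0.5 (CBT; the sign is immaterial). The grand mean is 0.125. The CBT row mean and the post-test column mean are both 0.25. The interaction effect in the CBT post-test cell is 0.5 − 0.25 − 0.25 + 0.125 = 0.125, and the other three cells are ±0.125. Hence f = d/4 = 0.125. Conversely, f = 0.25 needs d = 4 × 0.25 = 1.0 SD difference in change.

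**3. Power of the pre/post interaction at N = 44.**
- f = 0.25: λ = 0.0625 × 44 × 2/0.7 = 7.86, df 1 and 42, power 78.2%.
- f = 0.125: λ = 0.015625 × 44 × 2/0.7 = 1.96, power 27.8%.

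A t test on change scores is the same test: its noncentrality is 0.5/√(2 × 0.7) × √(22/2) = 1.40, whose square is 1.96. A simulation of 20,000 trials gave 27.6% for d = 0.5 and 78.7% for d = 1.0.

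**4. Four-visit interaction, constant 0.5 SD after baseline.** The arm differences are 0, 0.5, 0.5, 0.5, with mean 0.375. Half-deviations are −0.1875 and three times 0.0625, so f² = (0.03516 + 3 × 0.00391)/4 = 0.01172 and f = 0.108. Then λ = 0.01172 × 44 × 4/0.7 = 2.95, df 3 and 126 (ε = 1), power 26.3%. Other profiles peaking at 0.5 SD gave about 20% to 34%.

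**5. Other analyses of the same data, d = 0.5, 22 per arm.**
- Post-test only: noncentrality 0.5 × √11 = 1.66, power 36.7%.
- ANCOVA at one post-test: residual SD √(1 − 0.09) = 0.954, noncentrality 1.74, 41 df, power 39.7%.
- ANCOVA on the mean of three post-baseline visits, sustained effect: residual variance (1 + 2 × 0.3)/3 − 0.09 = 0.443, SD 0.666, noncentrality 2.49, power 68.2%.

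**6. Range and detectable effect.** Over the plan's own d = 0.4 to 0.6, power at 44 is 19.5% to 37.6% (pre/post interaction) and 27.4% to 53.1% (single post-test ANCOVA). If all 50 are analysed, d = 0.5 gives 31.0% and 44.3%. The effect detectable with 80% power at 22 per arm is 1.02 SD (pre/post interaction), 0.86 SD (post-test only) or 0.83 SD (ANCOVA). For d = 0.5, 80% power would need about 178 completers (interaction) or 118 (ANCOVA).

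**The case against.** The strongest reply is that the power statement is true of an interaction f of 0.25, and only its label as d = 0.5 is wrong. The article does not define d, and one of its sources, a residential programme, is described in the Background as a decrease compared with baseline, so some source values may be within-group changes. This stands as a reason to define d, but it does not rescue the figure: the text ties f = 0.25 explicitly to d = 0.5. If d is read in SDs of the change score, the pre/post test has 36.7% power (noncentrality 0.5 × √11).

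Second, the planned analysis is richer than pre/post. That also stands in part. A reader might infer that 28% to 40% is the power of every analysis the article allows. It is not. The range holds for one post-baseline measurement; baseline adjustment with three visits averaged and a sustained effect gives 68%, or 74% with all 50 analysed. At r = 0.7 the same analysis at 44 reaches 83%, against 55% (interaction) and 62% (ANCOVA) for pre/post. But r = 0.3 is the article's input, and this average is not the interaction test it names.

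Third, a reader might infer from the 46 in the two-measurement case that 44 is a miscalculation, or that two measurements must have been entered. The documents do not support either: three or four measurements with a plausible nonsphericity value give exactly 44, and an article commonly leaves such settings to the full protocol.

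Finally, a detectable effect of 0.83 to 1.0 SD lies around or below the d = 0.9 to 1.7 that the Background reports for reference 12. This softens the consequence if such effects are realistic, but the sample size rests on 0.5.

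**Conclusion.** The point holds. The two-group f for d = 0.5 is used for an interaction, and no reading tried of the named test with d = 0.5 and r = 0.3 reaches 80%. At 44 completers the power is about 28% for the pre/post interaction and about 26% for the four-visit interaction with a constant effect. Outside the named test, a single baseline-adjusted post-test has about 40%, and the most favourable analysis examined at r = 0.3 has about 68%.

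These figures rest on d in cross-sectional SD units, no baseline difference, and the stated r. The equivalence of f = 0.25 with 1.0 SD holds for the pre/post case only; over four visits with a constant effect it would be 0.25/0.108 × 0.5, or about 1.15 SD.

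It would go too far to say that the trial has less than half its stated power under every analysis, or that the investigators intend to read a null result as no effect; nothing in the article says the latter. The size of 50 is not in itself an error. The error is the power claimed for it.

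**What to change.** Keep 50 patients and correct the Sample size paragraph of the protocol article:

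- Say what d refers to (between-arm difference or within-group change, and in which SD), and give the number of measurements and the nonsphericity value entered in G*Power.
- State that, in the pre/post case, f = 0.25 in the interaction test means a difference in change of about 1.0 SD.
- Restate power at 44 completers for d = 0.5 as about 28% (pre/post interaction) or 40% (single post-test ANCOVA), and the effect detectable with 80% power as about 0.83 to 1.0 SD. If a repeated-measures comparison over several visits is meant to carry the trial, give its power and name it as the sized analysis.
- Reconcile the d = 0.4 to 0.6 attributed to reference 12 with the d = 0.9 to 1.7 reported for it in the Background.

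The cost is one rewritten paragraph and a less favourable power statement. No patient, visit or procedure changes.

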### Randomization

After providing informed consent and receiving a baseline assessment, the participating couples will be individually randomized. The allocation ratio for randomization into either the intervention or control condition is 1:1. The randomization will be performed by a computer algorithm independently operated by the Clinical Trial Centre of the University Hospital Zurich. The results of the randomization will be sent to the study nurse, who will telephone the participant and the caregiver to explain the next steps.

### Cognitive behavioural therapy intervention

#### Session content and setting

The CBT-based, multicomponent treatment programme consists of 25 sessions, mostly 60 mins in duration. The first two sessions (diagnosis and behaviour analysis) may take up to 90 mins. Table 1 details the content of all sessions. Most of them are joint sessions, but some are separate sessions with either the patient or the caregiver. The sessions of module 7 (interventions for the caregiver) are not prescribed by number, but as many are delivered as needed. They are conducted in parallel with sessions 4 to 16, with a variable time between the sessions starting after session 3. All sessions occur in rooms of the Psychiatric University Hospital Zurich, Department of Gerontopsychiatry, or at the outpatient clinic of the University of Zurich, Department of Psychopathology and Clinical Intervention.

**Table 1 Tab1:** Description of sessions

No	Topic	Therapeutic strategies	Setting
Module 1: Diagnosis and goal setting			
1	Diagnostic investigation	Diagnostic interview: comprehensive assessment of affective and behavioural symptoms, burden of caregiver, resources	Joint
2	Behaviour analysis and goal setting	Analysis of situation, behaviours, emotion, cognition, consequences; setting individual goals; planning interventions for joint and separate sessions	Joint
Module 2: Psychoeducation			
3	Psychoeducation	Providing information regarding disease, course, cause, medication, psychosocial interventions, support possibilities; adopting external memory aids (notebook, lists, signs for orientation, etc.); introducing mood journal	Joint
Module 3: Engagement in pleasant activities			
4	Setting the stage for pleasant activities	Explaining relation of behaviour (e.g., inactivity), mood (e.g., depression), neuronal degeneration and cognitive decline; developing a personal list of pleasant activities; introducing activity journal	Joint
5	Planning of pleasant activities	Selection of pleasant (social, physical, leisure) activities; planning of pleasant activities in a structured weekly schedule	Possibly without caregiver
6	Establishing regular activities	Discussing problems and progress with regular pleasant activities; motivation strategies to form habits (reinforcing by rewards; positive self-talk); introducing thought journal	Joint
Module 4: Cognitive restructuring			
7	Setting the stage for cognitive restructuring	Assessing typical negative (depression, anxiety, or anger related) and positive thoughts; completing the event–thought–emotion schema on the basis of recent examples; finding alternative thoughts	Joint
8	Challenging negative thoughts	Repetition of event–thought–emotion schema; challenging dysfunctional thoughts; repetition of finding alternative thoughts; describing thought control techniques (card and signal techniques)	Possibly without caregiver
9	Practising helpful thoughts	Discussing problems and progress with thought control techniques; strategies for practising helpful thoughts; introducing life review: structure and tools (e.g., photographs)	Joint
Module 5: Life review			
10	Childhood	Reminiscence of positive experiences in childhood	1 or 2 sessions joint, 2 or 3 sessions without caregiver
11	Adolescence	Reminiscence of positive experiences in adolescence	
12	Young adulthood	Reminiscence of positive experiences in young adulthood	
13	Older adulthood	Reminiscence of positive experiences in older adulthood; integration: review significant successes, reframe difficult times	
Module 6: Training caregiver in behaviour management techniques			
14	Setting the stage for behaviour management	Identifying problem behaviours, their precursors and consequences; describing the techniques: planning and implementing an intervention; evaluating an intervention; providing the caregiver (and patient) with methods to change precursors and consequences of behaviour (part 1)	Joint
15	Changing problem behaviour, part 1	Discussing the methods to change precursors and consequences of behaviour (part 1); discussing progress; discussing methods to change precursors and consequences of behaviour (part 2)	Joint
16	Changing problem behaviour, parts 2 and 3	Discussing progress; discussing the methods to change precursors and consequences of behaviour (part 3) (or repetition of behaviour parts 1 and 2)	Possibly without patient
Module 7: Interventions for the caregiver (parallel to sessions 4–16)			
i	Stress management and emotion regulation	Analyzing stressors, thoughts, emotional and behavioural reactions; self-monitoring of thought and behaviour; training in problem solving, cognitive reframing, relaxation techniques	Only caregiver
ii	Pleasant activities	Developing a personal list of pleasant activities; keeping an activity journal; selection of pleasant (social, physical, leisure) activities; planning of pleasant activities in a structured weekly schedule; discussing problems and progress with regular pleasant activities	Only caregiver
iii	Social support	Analyzing social support network; acceptance of formal and informal support (including cognitive restructuring); strategies of utilization of social support; communication with others about burden	Only caregiver
iv…		Approximately four sessions, but as many as needed	Only caregiver
Module 8: Couples counselling			
17	Setting the stage for couples counselling	Analyzing emotions regarding relationship, wishes, expectations, fears, typical conflicts, etc.; identifying core problems; oral history interview	Joint
18	Communication and joint problem-solving training	Improving communication style (roles as speaker and listener), training communication sequences; identify old and new coping strategies; establishing joint activities; maintaining important elements	Joint
19	Acceptance and planning for the future	Gradually challenging the view that everything is continuing normally; adapting to new roles (dependence, responsibility); joint planning of future care with a discussion of uncertainties and worries experienced by patient and caregiver	Joint
Closing of therapy			
20	Summary and reflection	Goal attainment scaling; evaluation of strategies; future planning	Joint

#### Therapeutic techniques

The majority of the therapeutic techniques stem from the CBT literature, including behaviour analysis, psychoeducation, advice on establishing pleasant activities, guidance on self-reward to motivate oneself, cognitive restructuring through Socratic dialogue and guided discovery, training in behaviour management, problem solving and stress management. The life review, though not a CBT technique in origin, is used in a highly structured variant to fit into the general CBT approach. The techniques in the couples counselling sessions, which do not belong to traditional CBT either, mainly include adopted behavioural strategies, i.e., training in communication and problem solving, planning and cognitive restructuring.

#### Psychotherapists

The CBT treatment programme will be administered by trained psychotherapists with a master’s degree in psychology or medicine and a qualification in CBT. Furthermore, all participating psychotherapists will be trained for this novel intervention by a panel of experts and supervisors in the field of CBT for older age (SF and AM). A 2-day workshop will precede the intervention phase. Supervision sessions will take part every month (i.e., about five sessions per patient). All sessions will be documented in a structured form and reflected upon in the supervision sessions.

#### Standardization of procedures

The therapeutic strategies and material for each session will be available in written form to all participating psychotherapists. Adherence to the treatment manual is ensured by the intensive training before the intervention phase, by regular supervision and by controlling the session documentation.

### Outcome measures

#### Primary outcome measures for a person with Alzheimer’s disease

The primary outcome measure will be level of depression in the patient with Alzheimer’s disease. Depressive symptoms will be measured using a short form of the Geriatric Depression Scale [56] and the Cornell Scale for Depression in Dementia [57]. Depressive disorders will be assessed using the Structured Clinical Interview for DSM-IV Axis I Disorders [58]. The diagnosis of depression is based on the criteria for major and minor depression of the Diagnostic and Statistical Manual of Mental Disorders IV (Text Revision) [59] and on the provisional diagnostic criteria for depression in Alzheimer’s disease [60]. Both the Cornell Scale for Depression in Dementia and the Geriatric Depression Scale are widely used; while the Geriatric Depression Scale is most appropriate for pre-clinical and mild dementia, the Cornell Scale for Depression in Dementia can also be applied when the severity of dementia is increasing.

